##### Impulsive behaviors

Checklist for Impulsive Behaviors (CIB)

This CIB is an ad hoc 15-item checklist created to determine the frequency of impulsive behaviors: alcohol use (4 items), substance use (2 items), internet addiction (4 items), gambling (1 item), non-suicidal self-injury (2 items), unprotected sex (1 item), and binge eating (1 item). Participants will be asked to indicate, on a 5-point Likert scale, the frequency of impulsive behaviors that occurred in the previous month (never; only once a week; two or three times a week; at least 4 times a week). Moreover, the checklist includes a section to evaluate the lifetime frequency of each behavior on a 6-point Likert sale (1–2 times, 3–5 times, 6–9 times, 10–19 times, 20–39 times, at least 40 times). For our primary outcome analysis, we will assess the difference between the two groups in the proportion of participants categorized as “improved” at post-intervention. Specifically, we will consider as “improved” those participants with a difference of at least one category toward improvement from baseline to post-intervention in the frequency of impulsive behaviors. Intervention efficacy will be established by treatment success, defined as at least 13% (i.e., 2/15 item) between groups after the intervention.

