### Outcomes {12}

#### Primary outcomes

##### Emotional regulation skills

DBT-Ways of Coping Checklist (DBT-WCCL) [45]

The DBT-WCCL is a 59-item self-report questionnaire measuring the frequency of DBT skills use (DBT Skills Subscale, 38 items) and dysfunctional coping strategies (Dysfunctional Coping Subscale, 21 items). Participants will be asked to indicate, on a 4-point Likert scale, the frequency of use of each skill in the previous month (i.e., never used, rarely used, sometimes used, or regularly used). The scale showed good internal consistency (Cronbach’s alpha coefficients for the subscales ranged from .84 to .96) and content validity [45]. For our primary outcome analysis, we will assess the difference between the two groups in terms of the proportion of participants categorized as “improved” post-intervention. Specifically, we will consider as “improved” those participants with a difference of at least one category, toward improvement, from the baseline to post-intervention in the frequency of use of functional skills. Intervention efficacy will be defined by a difference of at least 20% (i.e., 12/59 items) of improvement between groups after the intervention.

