### Sample size {14}

The primary outcome measures will be represented by changes in impulsive behaviors (established by the Checklist for Impulsive Behaviors) and by changes in emotional regulation skills (determined by the DBT-Ways of Coping Checklist).

Precisely, the outcome will be evaluated in terms of change (pre/post) in percentage of “yes” answers in the two groups (treated and control), where “yes” is defined as a difference of at least one category toward improvement from baseline. More specifically, the scores of the Checklist for Impulsive Behaviors are measured on a Likert scale. Therefore, a “yes” answer implies a decrease in the frequency of impulsive behavior; for example, from the category “two or three times a week” to the category “one time a week.” In a similar manner, a “yes” answer for the DBT-Ways of Coping Checklist means a decrease in the use of dysfunctional skills; for example, from the category “regularly used” to “sometimes used,” or vice versa for functional skills.

We assumed that at baseline, there would be a between-group difference by chance of 7% (i.e., 1/15 yes answers, where 15 is the total number of checklist items) on the Checklist for Impulsive Behaviors and that this difference would increase by up to 13% (i.e., 2/15 yes answers) after the intervention. Based on these assumptions and applying a two-sided test for paired binomial proportions, with a significance level equal to 0.05 and a power of 0.8, the estimated sample size was *n* = 340 (170 per group). Moreover, considering a drop-out rate of 20%, the minimum sample size (MSS) reached *n* = 426 (213 per group).

In the same way, we assumed that on the DBT-Ways of Coping Checklist, there would be a difference by chance of 7% (i.e., 4/59 yes answers, where 59 is the total number of the checklist DBT items) at baseline, and that this difference would increase by up to 20% (i.e., 12/59 yes answers) after the intervention. This last hypothesis was made considering that, given the focus of treatment, we expected a greater change in emotional regulation skills than in dysfunctional behaviors. Based on these considerations and applying a two-sided test for paired binomial proportions, with a significance level equal to 0.05 and a power of 0.8, we reached an estimated sample size of *n* = 84 (42 per group).

In sum, due to both the outcome measures and related sample size estimations, the final sample size needed was 426 students.

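### Efficacy requires a between-group difference of 13% or 20%, the same values the sample size assumes, so at the planned effect the rule is met about half the time, not 80%

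*Protocol article*

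**What the plan says.** Under Outcomes {12}, each primary outcome is a comparison of the proportion of students classed as improved. For the CIB, "we will assess the difference between the two groups in the proportion of participants categorized as “improved” at post-intervention". Each outcome then has its own definition of efficacy:

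- DBT-WCCL (Emotional regulation skills): "Intervention efficacy will be defined by a difference of at least 20% (i.e., 12/59 items) of improvement between groups after the intervention".
- CIB (Impulsive behaviors): "Intervention efficacy will be established by treatment success, defined as at least 13% (i.e., 2/15 item) between groups after the intervention".

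Sample size {14} uses the same figures as planning values. For the CIB it assumes "there would be a between-group difference by chance of 7% (i.e., 1/15 yes answers") at baseline and that "this difference would increase by up to 13% (i.e., 2/15 yes answers) after the intervention". For the DBT-WCCL it assumes that "there would be a difference by chance of 7% (i.e., 4/59 yes answers") at baseline and that "this difference would increase by up to 20% (i.e., 12/59 yes answers) after the intervention". Significance level 0.05 (two-sided) and power 0.8 give 170 per group for the CIB and 42 per group for the DBT-WCCL. The CIB figure rises to 213 per group after 20% drop-out.

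Statistical methods {20a} lists chi-squared tests and generalized mixed models, but does not link any of them to the efficacy definitions.

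**The concern.** A trial planned for 80% power should have about an 80% chance of reaching its stated criterion when the planning assumption is true. Here the power belongs to a significance test, while the stated criterion is a minimum size of difference. Because that minimum equals the assumed effect, the estimate has to land on or above its own expected value.

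Two things are at stake. First, the chance of declaring efficacy is well below what the sample size section leads a reader to expect. Second, the test and the efficacy definition can disagree, and the article does not say which one governs the primary conclusion. That choice would then be open after the data are seen.

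**Working it through.** **Inputs from the article.** Thresholds 13% (2/15) and 20% (12/59); planned values 13% and 20%; chance difference 7%; two-sided 0.05; power 0.8; 170 and 42 per group, 213 after drop-out.

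**Assumptions, because the article gives no figure.** The thresholds are percentage points of participants. The control-arm proportion improved is 5% to 40%. There is no clustering unless stated.

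**1. The plan's own figures.** A one-sample binomial formula with null p0 and alternative p1 reproduces both sizes:

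n = [(1.96·√(p0(1−p0)) + 0.8416·√(p1(1−p1))) / (p1−p0)]²

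- CIB, 0.07 against 0.13: [(1.96 × 0.2551 + 0.8416 × 0.3363) / 0.06]² = 170.4 (stated 170).
- DBT-WCCL, 0.07 against 0.20: [(1.96 × 0.2551 + 0.8416 × 0.4000) / 0.13]² = 41.4, rounded up to 42 (stated 42).
- Drop-out: 170 / 0.8 = 212.5, so 213 per group and 426 in all (stated 426).

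**2. What the 80% refers to.** In that formula the test rejects above p0 + 1.96·√(p0(1−p0)/n):

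- CIB: 0.07 + 1.96 × 0.2551/√170 = 0.108; power 0.80.
- DBT-WCCL: 0.07 + 1.96 × 0.2551/√42 = 0.147; power 0.80.

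The efficacy rule puts the bar at 0.13 and 0.20 instead.

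**3. Chance of meeting the rule when the planned effect is true.** In the normal approximation, P(D ≥ t) = 1 − Φ((t − δ)/SE). With δ = t this is 1 − Φ(0) = 0.50 whatever the SE, and so whatever the sample size. Exact two-arm binomial results:

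| Per arm | CIB, true 13 points | DBT-WCCL, true 20 points |
|---|---|---|
| 42 | 0.49–0.50 | 0.48–0.49 |
| 170 | 0.47–0.48 | 0.52–0.53 |
| 213 | 0.51 | 0.50–0.51 |

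Using the unrounded fractions 2/15 and 12/59 as the true effect, or the one-sample formulation, widens the range to 0.45–0.57. A design effect for classes (assumed ICC 0.01 to 0.05) leaves the CIB figure at 0.50–0.52, since it changes the SE but not the zero numerator.

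**4. Smaller true effects.** The article words 13% and 20% as upper values. For a true 10-point CIB difference with 170 per arm and a control rate of 20%, SE = √((0.2 × 0.8 + 0.3 × 0.7)/170) = 0.0467 and P = 1 − Φ(0.03/0.0467) = 0.26; the exact value is 0.24. Over control rates of 5% to 40% the exact range is 0.16 to 0.27.

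**5. Conflict with the test.** With 170 per arm and no clustering, the smallest difference that reaches two-sided 0.05 (pooled z-test) is about 6 points at a control rate of 5% and 10.6 points at 40%. A CIB difference between that limit and 13 points is significant, yet not efficacy by definition. With an assumed ICC of 0.05 and 17 per class, the design effect is 1 + 16 × 0.05 = 1.8 and the limits grow by √1.8 = 1.34, to about 8 and 14 points. At the upper end the conflict reverses: a difference of 13 points meets the rule without being significant. For the DBT-WCCL the limit stays below 20 points throughout.

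**The case against.** The strongest reply is that the article does not say the observed estimate alone decides. It names a two-sided test for planning and lists tests and mixed models for analysis, so 13% and 20% may be meant as targets or minimum relevant differences. Requiring a relevant difference is a legitimate choice, and calling a smaller effect insufficient is its purpose. This stands as a reason to keep the two values for interpretation. It does not rescue the text, which says efficacy is defined and established by them and attaches no test. Requiring significance as well would leave the chance of success the same or lower it.

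The units are also unclear: the thresholds are glossed as fractions of items, while the outcome is a proportion of participants. The calculation depends on the participant reading. The one-half result does not depend on the SE, but the figures for smaller effects do.

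Two stronger readings are tempting and are not supported:

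- A reader might take 7% and 13% as the two arms' rates, so that the planned difference is only 6 points and success is nearly impossible. The stated size does not support this. Comparing 7% with 13% in two arms needs about 391 per arm (7% with 20%, about 107), not 170 and 42, and the article calls the 7% a chance difference between groups.
- A reader might infer a family-wise error near 10% from two primaries, each at 0.05. That applies to two significance tests, not to the threshold rule. With no true effect, 170 per arm, no clustering and improvement rates up to 50%, the chance of meeting the threshold is at most about 0.7% (CIB) and 0.01% (DBT-WCCL). How the two primaries combine may also be settled in an analysis plan that is not shown.

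**Conclusion.** The point holds. The efficacy thresholds equal the planned effects, so the stated 80% power is not the chance of meeting the stated success rule. That chance is about 50% per outcome at the planned effect (0.45 to 0.57 across variants) at any sample size, and lower for any smaller true effect. The efficacy definition can also contradict the tests named elsewhere in the article, with nothing to say which prevails.

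The conclusion assumes that the thresholds are percentage points of participants and apply to the estimated difference. It does not depend on the unstated control rate, on clustering, or on how the sample size formula is interpreted. It does not extend to near-certain failure or to an inflated type I error.

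**What to change.** In both primary-outcome paragraphs of Outcomes {12}, replace the efficacy sentence along these lines: *Efficacy will be concluded if the two-sided 95% confidence interval for the between-arm difference in the proportion improved, from the mixed model with class as the cluster, excludes zero in favour of the intervention. Differences of 20 (DBT-WCCL) and 13 (CIB) percentage points of participants will serve as benchmarks for judging relevance.* Statistical methods {20a} should name that model as the one supporting the efficacy conclusion.

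If 13% and 20% are kept as success thresholds, Sample size {14} should state that the chance of meeting each is about 50% at the assumed effect. With 170 per arm, an 80% chance would need a true difference of about 16.5 to 18 points (CIB) or 23 to 24 points (DBT-WCCL), for control rates of 7% to 40% without clustering.

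A sentence on how the two primaries combine is an optional clarification.

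The cost is a protocol amendment. Recruitment began in November 2019, and the article's amendment section requires notice to the Ministry of Health and the Ethics Committee and an upload to the registry. The change should be dated before anyone sees outcome data by arm. It also lowers the bar for the word efficacy, which is why the benchmarks should be reported beside the interval. No further participants or data are needed.

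### Both primary outcomes count improved students, but their success thresholds and sample-size inputs are shares of questionnaire items, and the stated group sizes come from a one-sample formula, not a two-group comparison

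*Protocol article*

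**What the plan says.** For the Checklist for Impulsive Behaviors (CIB), under Outcomes {12}, the primary analysis is at student level: "we will assess the difference between the two groups in the proportion of participants categorized as" improved. The success rule in the same paragraph is at item level: "Intervention efficacy will be established by treatment success, defined as at least 13% (i.e., 2/15 item) between groups after the intervention". The DBT-Ways of Coping Checklist (DBT-WCCL) follows the same pattern. Its analysis compares proportions of participants improved, and its rule reads "Intervention efficacy will be defined by a difference of at least 20% (i.e., 12/59 items) of improvement between groups after the intervention".

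Sample size {14} describes the outcome as a pre/post change in the percentage of yes answers. For the CIB it assumes a "between-group difference by chance of 7% (i.e., 1/15 yes answers, where 15 is the total number of checklist items") and that "this difference would increase by up to 13% (i.e., 2/15 yes answers) after the intervention". For the DBT-WCCL it assumes 7% (4/59) rising to 20% (12/59). The method is given as "applying a two-sided test for paired binomial proportions", "with a significance level equal to 0.05 and a power of 0.8". The results are 340 students (170 per group) for the CIB, raised to 426 (213 per group) for 20% drop-out, and 84 (42 per group) for the DBT-WCCL.

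**The concern.** A share of students and a share of items are different variables. The first depends on how many students cross a line. The second depends on how many answers move within each student. The protocol treats them as equivalent, but it gives no rule for how many items, or what score change, make a student count as improved.

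Two things are at stake. First, the success rule for both primary outcomes has two readings that can disagree, and the choice could be made after the data are seen. Second, the power of 0.8 is the trial's only power statement, and it is attached to item-derived percentages and a calculation that is not the between-group comparison defined under Outcomes.

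**Working it through.** **1. The two units are not interchangeable.** Suppose the experimental group has 13 percentage points more improved students, each of these extra students improves on j of the 15 CIB items, and the groups are otherwise alike. The difference in mean item share is then 0.13 × j/15. With j = 1 it is 0.9 points, with j = 2 it is 1.7 points, and it reaches 13 points only when j = 15. A result can therefore meet 13% on students and miss 2/15 on items. The reverse can also happen: if nearly all students in both groups count as improved, a two-item advantage need not change the proportion improved.

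**2. The item set also varies.** The DBT-WCCL definition of improvement covers functional skills only, a 38-item subscale. The threshold uses 59 items, and Sample size {14} counts dysfunctional items as well. Twelve items are 20.3% of 59 but 31.6% of 38.

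**3. Reproducing the stated group sizes.** Inputs from Sample size {14}: two-sided 0.05 (z = 1.960), power 0.8 (z = 0.842), p0 = 0.07, p1 = 0.13 or 0.20. One-sample formula:

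n = [1.960·√(p0(1−p0)) + 0.842·√(p1(1−p1))]² / (p1−p0)²

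- CIB: (0.5001 + 0.2830)² / 0.06² = 170.35; stated 170 per group.
- DBT-WCCL: (0.5001 + 0.3366)² / 0.13² = 41.43, rounded up to 42; stated 42 per group.
- Drop-out: 170/0.8 = 212.5, rounded up to 213; doubled, 426.

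Other two-sided formulas on the same percentages do not give both figures:

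| Formula | CIB | DBT-WCCL |
|---|---|---|
| Two-sample, per group | 392 | 108 |
| Arcsine, per group | 384 | 102 |
| McNemar, the percentages as discordant cells, pairs | 434 | 123 |
| Paired margins, zero correlation, pairs | 394 | 110 |

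Paired margins with the exact fractions and an assumed correlation of 0.5 come near the CIB figure (169.7) but not the DBT-WCCL figure (58.4). The stated numbers therefore match a test of one group against a fixed 7%, used as the size of each of two groups.

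**4. The comparison that Outcomes {12} defines.** Two-sample formula for student proportions a and b, with mean m, before any allowance for clustering:

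n per group = [1.960·√(2m(1−m)) + 0.842·√(a(1−a)+b(1−b))]² / (b−a)²

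- 7% vs 13% of students: (0.8315 + 0.3553)² / 0.06² = 391.3, so 392 per group. Power at 170 per group is 45%.
- If 13% and 20% are differences between groups, the control improvement rate is needed. The protocol does not give it, so it is varied here as an assumption:

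| Control improved | 13 points: n per group | Power at 170 | 20 points: n per group | Power at 42 | Power at 170 |
|---|---|---|---|---|---|
| 7% | 108 | 94% | 55 | 69% | >99% |
| 20% | 180 | 78% | 82 | 52% | 98% |
| 40% | 230 | 67% | 97 | 45% | 96% |
| 43.5% | 232 | 67% | 97 | 45% | 96% |
| 70% | 166 | 81% | 62 | 63% | >99% |

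The 170 evaluable per group follows from the planned total: 426 × 0.8 / 2 = 170.4.

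**The case against.** The strongest defence is that 170 per group may be adequate. A 13-point difference with about 18% of controls improving (18% vs 31%) needs 171 per group, almost exactly the stated figure. This stands. A reader might infer that the trial is shown to be underpowered, or that 170 is ruled out on either scale. The document supports neither, because it gives no control rate. On items, 7% vs 13% of 15 items needs anywhere from 26 to 389 per group as the assumed inter-item correlation runs from 0 to 1.

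A second defence is that the one-sample formula treats 7%, 13% and 20% as shares of students, so the sizing is already at student level. That is correct as far as it goes. It also means that the sizing fault is not the binomial variance of an item share carried over to students, as a reader might suppose. But the percentages are derived from item counts, and the formula compares one group with a fixed value.

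A third is that scoring a student as improved on any single item would convert the units. That is one possible rule, but the protocol does not state it, so student-level differences computed from it are illustrations only.

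Finally, an article condenses, and an analysis plan may add detail. This point is not an omission, however: the article itself states the outcome, the thresholds and the sizing in units that do not agree.

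**Conclusion.** The point holds as a contradiction of units, together with a sample-size calculation that does not match the stated comparison. It affects both primary outcomes, both success thresholds and the power statement.

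The size of the power error depends on what the 13% means. Read as 7% vs 13% of students, 170 per group gives about 45% power. Read as a 13-point difference, it gives between about 94% and 67% over an assumed control rate of 7% to 70%. The direction is therefore undetermined. For the DBT-WCCL, 42 per group is below the 55 to 97 that a 20-point difference needs over the same range. The trial is sized on the CIB, however, so power for that outcome at 170 per group stays at about 96% or more, and a shortfall there should not be inferred. All figures assume independent students; clustering by class is a separate matter and is not included.

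**What to change.** Use the student as the unit in both primary-outcome paragraphs and in Sample size {14}, as the stated primary analysis already does.

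- Delete the item equivalents (12/59 and 2/15) and state both thresholds as percentage points of students.
- State the item count or score change that makes a student improved. For the DBT-WCCL, apply it to one item set: the 38 functional items or all 59.
- Replace the one-sample calculation with a two-group comparison of student proportions under a stated control improvement rate.
- Restate the power that the planned 426 students (about 170 evaluable per group) deliver.

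The change itself costs wording in three places and a recalculation, with no new data. The downside is that the restated power may be less favourable. Whether 426 students are enough can be judged only after the recalculation, so it should not be promised that no more will be needed.

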#### Secondary outcomes

Secondary outcomes will be assessed in terms of differences in the mean score between baseline and post-intervention on the instruments measuring the following domains:

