### Objectives {7}

The aim of the present study is twofold. The first is to evaluate the impact of a school-based intervention focused on emotional regulation strategies in a sample of adolescent students. The primary outcome will be changes in the frequency of use of emotional regulation skills and changes in the frequency of impulsive behaviors. Our hypothesis is that (1) at the end of intervention, the students who received the intervention will report a reduction in the frequency of impulsive behaviors compared to baseline, whereas we expect no differences in the group of adolescents who will not receive the intervention; (2) at the end of intervention, the students will report an increase in the use of emotional regulation skills compared to baseline, while we expect no differences in the control group; and (3) these changes will be maintained at 3 and 6 months of follow-up.

The second aim was to assess the association between biological features and ED in adolescent students. Specifically, we will compare several biomarkers related to stress response and inflammation in subgroups of students with different levels of ED assessed with the Difficulties in Emotion Regulation Scale (DERS) [4] measured at baseline. Moreover, the repeated collection of salivary samples post-intervention will allow us to evaluate the role of these biological features in the interventions’ effects on the behavioral variables described above (i.e., impulsive behaviors and use of skills).

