### Trial design {8}

This is an interventional, parallel assignment, two-arm, cluster randomized trial. The classes of students will be randomized into a psychoeducational intervention (experimental group) or control condition (control group). All participants will be assessed at baseline, post-intervention, and at the 3- and 6-month follow-up points by using self-report questionnaires. In addition, salivary samples will be collected at baseline and post-intervention. Details on the timeline and assessments are reported in Table 1.

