##### Problem-solving style

Social Problem-Solving Inventory-Revised Short Form (SPSI-R:SF) [46, 47]

The SPSI-R:SF is a 25-item, self-report questionnaire measuring abilities in problem-solving: positive problem orientation (PPO), negative problem orientation (NPO), rational problem-solving (RPS), impulsivity-carelessness style (ICS), and avoidant style (AS). Each item is rated on a 5-point Likert scale, and scores are computed for each of these subscales, as well as a global score for total inventory. Higher scores on the NPO, ICS, and AS reflect a more maladaptive approach to problem-solving, whereas higher scores on the PPO and RPS indicate more adaptive strategies. Studies have reported good construct validity, internal consistency (with Cronbach’s alpha coefficients ranging from .73 to .86), and test–retest reliability (with the intraclass correlation coefficients ranging from .74 to .87) [46, 47].

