## Statistical methods

### Statistical methods for primary and secondary outcomes {20a}

Descriptive statistics (frequencies and percentages for categorical variables, and means and standard deviations for continuous variables) will be evaluated. To compare categorical variables, the chi-squared test will be used. To compare continuous variables between the different groups of interest, *t*-tests, ANOVA, or corresponding non-parametric tests (Mann–Whitney or Kruskal–Wallis) will be performed. Moreover, generalized mixed models will be harnessed to assess the differences in dysfunctional behaviors and emotional regulation skills across time and between groups (including post hoc analyses).

Differences in the levels of the biomarkers will be assessed by using linear and generalized linear models adjusting for potential confounders such as sex. Correlations (Pearson or Spearman) and generalized linear models will be employed to assess the association between the level of emotional dysregulation and other clinical variables and biomarkers.

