### Methods for additional analyses (e.g., subgroup analyses) {20b}

Analyses for primary and secondary outcomes will include (i) subgroup evaluation through post hoc analysis and (ii) adjustment for potential confounders, so no further additional analyses will be performed.

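### Secondary scales are fixed as baseline-to-post mean differences and left to simple group tests; a baseline-adjusted model with class as a random effect would be more precise and fit the design

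*Protocol article*

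**What the plan says.** The Secondary outcomes section introduces the problem-solving, emotional dysregulation (DERS), depression, anxiety and impulsivity scales with one definition: "Secondary outcomes will be assessed in terms of differences in the mean score between baseline and post-intervention". It names no contrast between arms. The two primary outcomes are each worded as a difference between groups.

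Section {20a}, whose heading covers primary and secondary outcomes, sets out two routes:

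- For continuous scores it lists t-tests, ANOVA or rank-based equivalents, introduced by "To compare continuous variables between the different groups of interest".
- For the longitudinal comparison it says "generalized mixed models will be harnessed to assess the differences in dysfunctional behaviors and emotional regulation skills across time and between groups". Under Outcomes and Sample size, emotional regulation skills means the coping checklist (DBT-WCCL). The DERS has its own heading among the secondary outcomes, so the model is named for the primary domains.

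Section {20b} adds: "Analyses for primary and secondary outcomes will include (i) subgroup evaluation through post hoc analysis and (ii) adjustment for potential confounders". It does not say which confounders; the one example in {20a}, given for biomarkers, is sex.

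Trial design {8} calls this a cluster randomised trial of classes and says "All participants will be assessed at baseline, post-intervention, and at the 3- and 6-month follow-up points by using self-report questionnaires". Sequence generation {16a} allocates classes 1:1 within each school, and Study setting {9} plans 20 classes.

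**The concern.** Taken together, these sections point to a secondary analysis that computes change from baseline to post-intervention for each student and compares the arms with a t-test or similar. That has three weaknesses.

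1. **Precision.** Subtracting the baseline in full is efficient only when baseline and post scores are almost perfectly correlated. Using the baseline as a covariate is never worse in large samples and is usually better.
2. **Imbalance.** If the arms differ at baseline by chance, the arm with the higher starting score is expected to fall further through regression to the mean. A change score credits or debits that drift to the intervention. With about 10 classes per arm, some imbalance is plausible even with allocation within school.
3. **Clustering.** Classes are randomised, but a t-test, ANOVA or rank test on students treats them as independent. The planned mixed model could carry class, yet it is not named for these scales.

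At stake is the quality of the evidence on the secondary scales, including the DERS, the trial's direct measure of emotional dysregulation. The primary efficacy criteria do not depend on it.

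**Working it through.** **The plan's own figure.** The article gives no sample size or precision figure for any secondary scale. Its total of 426 is for the impulsive-behaviour checklist: 170 / (1 − 0.20) = 212.5, rounded up to 213 per arm, and 2 × 213 = 426. This reproduces. It bears on this point only by supplying 170 evaluable students per arm.

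**Inputs**

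- Correlation r between baseline and post scores: not stated. Proxy: the problem-solving scale's test-retest "intraclass correlation coefficients ranging from .74 to .87". The retest interval is not given, and here four monthly sessions lie between baseline and post, so r may be lower. I add r = 0.5 as an assumption.
- Students per arm: 170.
- Error rates from Sample size {14}: two-sided 0.05 and power 0.80, so z values 1.960 + 0.842 = 2.802.
- Assumed: equal SD at both visits, a linear relation with the same slope in both arms, and no clustering.

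**Formulas** (in units of SD²)

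- Variance of a change score: 2(1 − r).
- Variance of a baseline-adjusted score: 1 − r².
- Adjusted as a share of change: (1 + r)/2. Extra participants needed by the change score: 2/(1 + r) − 1.
- Minimum detectable difference: 2.802 × √(2 × variance / 170).

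**Results**

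| r | Variance, change | Variance, adjusted | Share | Extra participants | Detectable, change | Detectable, adjusted |
|---|---|---|---|---|---|---|
| 0.87 | 0.26 | 0.2431 | 0.935 | 7% | 0.155 SD | 0.150 SD |
| 0.74 | 0.52 | 0.4524 | 0.87 | 15% | 0.219 SD | 0.204 SD |
| 0.5 (assumed) | 1.00 | 0.75 | 0.75 | 33% | 0.304 SD | 0.263 SD |

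For r = 0.74: 2/1.74 = 1.149, and 2.802 × √(2 × 0.52/170) = 0.219 against 2.802 × √(2 × 0.4524/170) = 0.204.

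**Imbalance.** If the arms differ by δ at baseline, the change score removes δ in full, while the regression removes rδ. The over-correction is (1 − r)δ: 13% of the baseline difference at r = 0.87, 26% at 0.74 and 50% at 0.5.

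**Class.** The article gives no intraclass correlation for class. With 22 students per class, the design effect 1 + (22 − 1) × ICC is 1.21 at an assumed ICC of 0.01 and 2.05 at 0.05. This is the factor by which a test ignoring class could understate the variance of the arm difference. It is illustrative only: the ICC of a change score may differ, and allocation within school offsets part of it.

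**The case against.** The best defence is that much of what seems missing is present or belongs elsewhere.

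- **A between-arm comparison exists.** A reader could infer from the Secondary outcomes wording, and from hypotheses phrased as change within each group, that the arms are never compared on these scales. The article does not support that: {20a} gives between-group tests for continuous variables under a heading that includes secondary outcomes, and {20b} promises confounder adjustment for them.
- **Follow-up scores cannot be called unused.** Trial design {8} has questionnaires completed at 3 and 6 months but does not say which. Table 1, which would say, is not reproduced in the text at hand. If a scale stops at post-intervention, its definition simply matches the schedule.
- **The maintenance hypothesis does not reach these scales.** In Objectives {7}, "these changes will be maintained at 3 and 6 months of follow-up" refers back to impulsive behaviours and skills use. Both are primary and are covered by the mixed model.
- **The gain is modest.** At the only correlation given, the detectable difference moves by 0.015 SD or less, and the student-level formula does not carry over directly to 20 classes.
- **A change score is not biased.** Over repeated randomisation it estimates the same effect, and a covariate list is commonly left to an analysis plan.

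All of these stand and limit the point. They do not remove it. The article does more than stay silent: it defines the secondary outcome as a pre-post difference and assigns continuous scores to tests that, as described, carry neither baseline nor class. It already plans a better model for other outcomes. An analysis plan using that model for these scales would depart from the definition as written.

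**Conclusion.** The point holds as an improvement to how the secondary outcomes are defined and analysed. As written, the route leads to an unadjusted change-score comparison with no baseline covariate and no allowance for class.

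The precision cost is equivalent to about 7 to 15% of participants if r lies in the test-retest range of one secondary instrument. It is 33% only if r is as low as 0.5, which is an assumption. These are student-level figures that ignore clustering, so the realised gain may differ. They apply only if the baseline is not among the unspecified confounders of {20b}. In addition, a change score over-corrects any chance baseline difference by a fraction 1 − r.

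The point does not extend to a missing between-arm comparison, to wasted 3- and 6-month data or to an untested maintenance hypothesis.

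**What to change.** Restate each secondary outcome as the between-arm difference in mean score at post-intervention. Estimate it with the mixed model already planned in {20a}, with baseline score and school as covariates and class as a random effect.

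For any secondary scale that Table 1 repeats at 3 and 6 months, enter the three post-baseline visits as outcomes with arm, visit and arm-by-visit terms, add a student random effect, and report the difference at each visit. For any scale not repeated, state that its outcome ends at post-intervention.

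The cost is a revised definition and a little analysis time. No new measurement is needed, because the present definition already requires baseline and post scores and the extra visits are added only where scheduled. It is more than an edit to the text, though: under the amendments section {25}, the Ministry of Health and the Ethics Committee must be told of protocol changes, and authorised changes are posted to the registry. The rewording should be settled before the arms are compared.
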